**Abstract**

*Background:* Multi-component CS programs incorporating practice of activities of daily living (ADL) into intervention have reported benefits for ADL outcomes in individuals living with mild-to-moderate dementia. A randomised controlled trial (RCT) within community occupational therapy services in Ireland, is planned to evaluate the effects of CS-ADL, an ADL-focused, multi-component CS program, on ADL outcomes for individuals living with mild-to-moderate dementia.

*Method:* A single-blind RCT with a calculated sample size of 34 participants has been planned to compare the effects of CS-ADL versus treatment as usual on the outcomes of basic ADLs and instrumental ADLs. Cognition, mood, communication, and quality of life will also be evaluated as secondary outcomes. CS-ADL sessions will run once weekly for a total of seven weeks, lasting approximately two hours each. Outcome data will be collected at baseline, within sessions and post-intervention at week eight. Descriptive statistics will be used to analyse the data.

*Discussion:*  CS programs are commonly conducted by occupational therapists working with individuals living with mild-to-moderate dementia. This study aims to demonstrate the effectiveness of a multi-component CS program delivered through an occupational therapy lens, potentially influencing the approach to CS and ADL interventions undertaken by occupational therapists.

**Introduction**

Dementia is a clinical syndrome characterised by deteriorating cognitive, behavioural and emotional functions that interfere with an individual’s performance in activities of daily living (ADL; American Psychiatric Association, 2013; Dolan and Shiel, 2017). The cognitive and social changes associated with the condition have been linked to decreased quality of life, increased caregiver burden, and higher care costs, contributing to dementia being one of the leading causes of hospitalisations and admissions to skilled nursing facilities worldwide (Laver et al., 2016). Dementia affects approximately 57.4 million people globally, with an estimated 53,932 individuals in Ireland living with dementia as of 2019 (Nichols et al., 2022; Pierse, Keogh and O’Neill, 2020). The widespread impact of dementia has prompted the development of a variety of treatments to slow the cognitive and functional decline associated with this condition (Arvanitakis, Shah & Bennett, 2019). Several non-pharmacological interventions are increasingly being used to mitigate this decline, with cognitive stimulation (CS) being one such approach.

CS is a non-pharmacological approach to intervention widely used with individuals with early-stage dementia. CS is typically delivered in a stimulating and rewarding environment, where participants engage in a range of activities and discussions aimed at enhancing global cognitive and social functioning, as opposed to a focus on specific functions in isolation (Clare and Woods, 2004). A variety of CS interventions have been described across the literature, including manualised therapies, individual programs, and CS delivered as part of a wider, multi-component intervention (Ryan & Brady, 2023). Cognitive stimulation therapy (CST) is one notable example of a manualised therapy commonly used by occupational therapists for people living with mild-to-moderate dementia. CST is a brief group intervention based on CS principles, consisting of 14 sessions of themed activities and discussions run over seven weeks (Spector et al., 2003). Several adaptations of this CST program have been developed and evaluated in the literature, including a 24-week maintenance program (MCST) and an individualised program (iCST). CST has demonstrated significant benefits for cognition, quality of life and communication for individuals with mild-to-moderate, as reported by Woods et al.’s (2012) systematic review. While it is assumed that cognitive improvements following CS interventions will transfer to everyday functioning, evidence from the literature does not support this assumption; no statistically significant effects of CS for ADL performance were reported (Woods et al., 2012).

However, Ryan & Brady’s (2023) scoping review exploring the use of CS in improving ADL outcomes for individuals with mild-to-moderate dementia mapped a variety of alternative CS programs that reported benefits for ADLs. Three randomised controlled trials (RCTs) with an overall total of 252 participants evaluated the effect of a German, multi-component group therapy termed MAKS (Graessel et al., 2011; Luttenberger et al., 2012a; 2012b). MAKS sessions consist of physical activities, individual/group cognitive stimulation exercises, and participation in ADL tasks, with all three studies reporting benefits of MAKS on ADL abilities. A cognitive-motor stimulation intervention (CMSI) was evaluated at 12 months by Olazarán et al. (2004) and at three years by Muñiz et al. (2015) through an RCT design. CMSI sessions consisted of individual/group cognitive exercises, psychomotor therapy, and ADL training. Favourable ADL outcomes were reported for the CMSI group when compared to a control. Furthermore, Jiménez Palomares et al.’s (2021) pilot RCT (*N=*58) investigating the effects of an occupational therapy CS program on ADL skills reported significant improvements in basic ADLs such as feeding, dressing and continence. Ryan and Brady’s (2023) scoping review observed a common trend across studies reporting positive effects for ADLs; multi-component interventions incorporating CS with ADL practice and/or physical activity produced more favourable ADL outcomes in comparison to traditional, discussion-based CS programs, like CST.

Occupational therapy is a profession where occupational performance and engagement in ADLs are central to intervention. While the nature of the scoping review methodology used by Ryan and Brady (2023) limits conclusions that can be drawn, the reduced evidence supporting the benefits of traditional CS programs for ADLs calls for a shift in approach used by occupational therapists. The incorporation of ADL-focused activities into multi-component CS programs demonstrate promising results for ADL outcomes (Graessel et al., 2011; Muñiz et al., 2015). However, the majority of multi-component CS interventions reported to benefit ADL outcomes by Ryan and Brady (2023) recruited participants from nursing homes or long-term care facilities. The lack of data evaluating the implementation of these programs within the community setting prompted the development of CS-ADL, a multi-component group CS program that aims to enhance ADL performance alongside social and cognitive functioning.

The CS-ADL program was scientifically developed based on the currently available literature evidence and appropriately revised after it was successfully piloted in an Irish, community-based Psychiatry of Later Life service. Previous qualitative research has explored the experience of taking part in CS-ADL, reporting that both participants and their caregivers perceive CS-ADL to be an acceptable intervention that positively influenced the daily lives of both dyad members with benefits reported in the memory, mood and social interaction of participants (Ryan, Chockalingam & Brady, 2023). However, CS-ADL is a newly developed intervention; no previous studies have explored the effectiveness of CS-ADL on improving ADL outcomes. Therefore, an RCT evaluating the effect of CS-ADL on ADL outcomes when compared to a group receiving treatment as usual (TAU) is proposed. This RCT will take place in Irish community occupational therapy services, and individuals living with mild-to-moderate dementia will be recruited to take part.

*Aims and objectives*

The aim of this study is to evaluate the effect of CS-ADL, an ADL-focused multi-component CS program, on ADL outcomes for people living with mild-to-moderate dementia. The primary objective of this study is to determine the effect of CS-ADL on basic ADL (BADL) and instrumental ADL outcomes (IADL). The secondary objectives of the study include examining the effects of the intervention on cognition, mood, quality of life (QOL) and communication. These secondary outcomes were chosen as previous CS programs have demonstrated benefits for these variables (Woods et al., 2012).

*Hypotheses*

*Null hypotheses*

CS-ADL does not benefit ADL outcomes in people with mild-to-moderate dementia when compared to TAU.

CS-ADL does not benefit cognition, mood, quality of life and communication in people with mild-to-moderate dementia when compared to TAU.

H_0_: µ_CS-ADL_ = µ_TAU_

*Alternate hypotheses*

CS-ADL benefits ADL outcomes in people with mild-to-moderate dementia when compared to TAU.

CS-ADL benefits cognition, mood, quality of life and communication in people with mild-to-moderate dementia when compared to TAU.

H_1_: µ_CS-ADL_ > µ_TAU_

**Materials and methods**

*Trial design*

This will be a multi-centre, parallel, single-blind, randomised superiority trial of CS-ADL versus TAU for people with mild-to-moderate dementia. Sample size was calculated using formal power analysis with G*Power software (Faul et al., 2007). Based on Cohen’s (1988) guidelines for small (*r =* 0.1), medium (*r* = 0.3) and large (*r =* 0.5) effects for a 2 (pre- and post-test) x 2 (CS-ADL and TAU) *t*-test, with the difference between two dependent means (matched pairs), sample size was calculated for an estimated small (*d =* 0.2), medium (*d* = 0.5) and large (*d* = 0.8) effect size. Two-tailed alpha of 0.05 was assumed for all tests. With an estimated effect size of 0.2, a sample size of 199 is required for a critical t of 1.9720175 and degrees of freedom (df) of 198, with an actual power of 0.8016910. With an estimated effect size of 0.5, a sample size of 34 is required for a critical t of 2.0345153 and a df of 33 and an actual power of 0.8077775. For an estimated effect size of 0.8, a sample size of 15 was calculated to be required for a critical t of 2.1447867 and a df of 14, with an actual power of 0.8213105. It is expected there will be challenges in the recruitment of 199 participant for the estimated effect size of 0.2, therefore for pragmatic reasons, recruitment will aim for the sample size of 34 (*d* = 0.5). Participants will be randomised with 1:1 allocation ratio to either the intervention or control group. The primary and secondary outcomes will be measured at baseline prior to randomisation and at the end of intervention (8 weeks). There will also be an observational assessment of occupational performance completed by the treating therapists within every group session.

*Study setting*

The study will take place in two Irish Health Service Executive (HSE), community-based occupational therapy services. The principal investigator will deliver the CS-ADL intervention.

*Eligibility criteria*

Eligibility criteria for this study reflects criteria of previous multi-component CS interventions. Participants must have a formal diagnosis of major neurocognitive disorder (dementia) as per the DSM-V criteria (American Psychiatric Association, 2013). Participants must have a mild-to-moderate cognitive impairment as classified by the Mini Mental State Examination (MMSE) or equivalent screens (Folstein et al., 1975). Individuals with severe dementia, i.e., an MMSE<10, will be excluded as most CS interventions are not applicable for those with severe cognitive impairment (Spector et al., 2003). Participants taking dementia medication can continue to do so during the study.

Participants must have some ability to communicate and understand communication, determined by a score of 1 or 0 on questions 12 and 13 of the Clifton Assessment Procedures for the Elderly-Behaviour Rating Scale (Pattie and Gilleard, 1979). Participants must be able to see and hear well enough to participate in the group. Participants will not be excluded if they have significant uncontrolled disruptive behaviours, a premorbid diagnosis of a learning disability, or a significant physical illness/disability that may affect participation during intervention sessions or assessments.

*Recruitment*

Participants will be recruited from HSE occupational therapy settings in Ireland. Clinicians will be encouraged to screen their case load for potential participants and approach them and their caregiver to discuss the study. If they are interested in taking part, internal referral protocols will be followed. Contact details will be passed to the research team who will arrange a meeting with the participant and their caregiver to assess eligibility. If they are eligible and agree to take part, informed written consent will be obtained. Participants’ capacity to consent to take part in the study will be assessed following the guidelines stipulated in the Assisted Decision-Making (Capacity) Act (2015). If the participant with dementia lacks the capacity to consent, appropriate protocols will be adhered to in line with the Assisted Decision-Making (Capacity) Act (2015) which is currently evolving into full enactment in Ireland.

*Randomisation and masking*

Randomisation will occur after eligibility, consent and baseline assessments have been carried out. Random allocation will be completed by an allocator otherwise uninvolved in the study. A computer-generated number system (RANDBETWEEN Command on Microsoft Excel) will be used. While participants cannot be blinded to their allocated group, outcome assessors will be blind to group allocation.

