The study sample will be analysed using descriptive statistics through the latest version of Statistical Package for Social Sciences (SPSS). Data on recruitment will be recorded and examined. A Consolidated Standards of Reporting Trials (CONSORT) diagram describing the flow of participants through the study will be presented in the final RCT report, detailing enrolment, allocation, follow-up, and analysis of data (Figure 1). Baseline data will be assessed for normality and if normally distributed, parametric analysis will be used. Where data is not normally distributed, non-parametric analysis will be used. Types of tests chosen will be based on whether the data is parametric or non-parametric. Significance levels will be set to 0.05. A linear regression model adjusting for baseline scores will be used to estimate the effect of intervention on each of the primary and secondary outcomes, with a between-group analysis completed to examine if the groups are significantly different at outcome. A within-group analysis will be also completed to evaluate if there are any significant changes within groups. Sociodemographic factors like age and gender will be entered as covariates.

*Ethical considerations*

The researchers are currently in the process of receiving ethical approval for this study.

*Anticipated risks for trial participants*

There appear to be no documented harmful side effects from participating in typical CS programs, with no adverse reactions apparent. Health and safety risks, including the risk of falls may be posed by the participation in cooking tasks and physical activities. However, group facilitators will use their clinical judgement, clinical risk assessments in the implementation of activities and always ensure adequate supervision is given. Nevertheless, potential participants and their caregivers will be fully informed of the potential risks before partaking in the trial.

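### The sample size of 34 comes from a matched-pairs t-test, but the trial compares two independent arms of 17, where power at d = 0.5 is about 0.29 unadjusted, not 0.81

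*Protocol*

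**What the plan says.** The Trial design section of the protocol describes a "multi-centre, parallel, single-blind, randomised superiority trial of CS-ADL versus TAU" with 1:1 allocation. The sample size, computed in G*Power, is for a t-test "with the difference between two dependent means (matched pairs), sample size was calculated" at small, medium and large effects. On alpha it says: "Two-tailed alpha of 0.05 was assumed for all tests". For the medium effect (d = 0.5) the protocol reports: "a sample size of 34 is required for a critical t of 2.0345153 and a df of 33 and an actual power of 0.8077775". The small and large effects (0.2 and 0.8) give 199 and 15. Recruitment of 199 is judged difficult, so 34 is adopted for pragmatic reasons.

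The Abstract shows that 34 is the size of the whole trial: "A single-blind RCT with a calculated sample size of 34 participants". The Hypotheses section sets the mean under CS-ADL against the mean under treatment as usual. The Statistical analysis section says "A linear regression model adjusting for baseline scores will be used to estimate the effect of intervention" on each outcome, with a between-group comparison at outcome and an additional within-group analysis.

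**The concern.** A matched-pairs test with 33 degrees of freedom treats all 34 people as a single group, each measured twice. It asks whether that group changed. It has no treatment factor, even though the protocol labels the calculation as a 2 x 2 of time by arm. The trial asks whether two separate, randomised groups differ. Nobody is matched across arms and nobody crosses over.

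For the same d, the comparison of two independent arms needs far more people, because each arm holds half the sample and both means carry error. If the power is overstated, the decision that 34 is enough for a medium effect was taken on a wrong table. A non-significant result could then be read as evidence against a benefit, on the strength of a sensitivity that the design does not have.

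**Working it through.** **Inputs.** From Trial design: two-sided alpha 0.05; d = 0.2, 0.5 and 0.8; N = 199, 34 and 15; 1:1 allocation. From the Abstract: 34 in total, hence 17 per arm. From Statistical analysis: regression adjusted for baseline. Assumed, because the protocol gives no value: the correlation r between baseline and week 8. All powers use the noncentral t distribution.

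**1. Reproduce the protocol's figures.** For a paired test, df = n − 1 and the noncentrality is d√n. For d = 0.5 and n = 34 this is 0.5 × √34 = 2.915 on 33 df.

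| d | n | df | Critical t | Power |
|---|---|---|---|---|
| 0.2 | 199 | 198 | 1.9720175 | 0.8016910 |
| 0.5 | 34 | 33 | 2.0345153 | 0.8077775 |
| 0.8 | 15 | 14 | 2.1447867 | 0.8213105 |

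All three rows agree with the protocol to every printed digit, so the test used is not in doubt.

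**2. The comparison between arms, unadjusted.** For two independent means with n per arm, df = 2n − 2 and the noncentrality is d√(n/2). For n = 17 and d = 0.5 this is 0.5 × √8.5 = 1.458 on 32 df, with critical t 2.037. Power is **0.293**. For d = 0.2 and 0.8 it is 0.087 and 0.619.

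**3. The planned analysis, adjusted for baseline.** Adjustment shrinks the residual SD by √(1 − r²), so the effective effect is 0.5/√(1 − r²), with 31 df.

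| Assumed r | Effective d | Power, d = 0.5 | Effect detectable at 80% (outcome SD) |
|---|---|---|---|
| 0.5 | 0.577 | 0.37 | 0.86 |
| 0.7 | 0.700 | 0.51 | 0.71 |
| 0.8 | 0.833 | 0.65 | 0.60 |
| 0.85 | 0.949 | 0.76 | 0.52 |
| 0.9 | 1.147 | 0.90 | 0.43 |

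Power of 0.80 is reached at r of about 0.86. Without adjustment, the effect detectable at 80% power is 0.99 SD. Adding age and gender as covariates takes two more df and changes little (0.507 becomes 0.505 at r = 0.7).

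**4. The within-arm test.** Each arm has 17 pairs: 0.5 × √17 = 2.062 on 16 df, power 0.49. The stated 0.81 does not fit this analysis either.

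**5. Size needed for 80% power, unadjusted two-arm test.**

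| d | Per arm | Total | Protocol |
|---|---|---|---|
| 0.2 | 394 | 788 | 199 |
| 0.5 | 64 | 128 | 34 |
| 0.8 | 26 | 52 | 15 |

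**6. Alternative readings.** If 34 were the number per arm, power would be 0.53. A one-sided test at 0.05 with 17 per arm would give 0.41. Neither reaches 0.81, and the Abstract and the two-tailed alpha rule them out.

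**7. Loss to follow-up.** The protocol states no allowance. With four people lost (15 per arm), 0.29 falls to 0.26.

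**8. Precision.** The unadjusted 95% interval has a half-width of 2.037 × √(2/17) = 0.70 SD.

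**The case against.** The strongest objection is that 0.29 is not the power of the planned analysis. The protocol adjusts for baseline, and a high enough correlation would bring power up to or past 0.80; nothing in the document caps the correlation at 0.8. This stands as a caution: 0.29 must be labelled as unadjusted and the adjusted figures as conditional on r. It does not rescue the stated figure, because the protocol's calculation uses no correlation and the agreement at about 0.86 would be a coincidence.

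The effect-size scales also differ. A paired d is in units of the SD of change, whereas the adjusted calculation uses the SD of the outcome, so the totals in step 5 are not a like-for-like comparison with the protocol's. This is fair. But if d = 0.5 is read as a difference between arms in change, in units of the SD of change, power with 17 per arm is again 0.29.

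The protocol's arithmetic is indeed exact; the fault lies in the choice of test. The protocol also does not say that a non-significant result will be reported as no benefit, so that risk concerns how the result might be read. The loss of four people is a small matter next to the main error. Finally, 34 was openly a pragmatic choice. That can justify a small trial, but not the power attached to it.

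**Conclusion.** The concern holds and must be corrected. The stated power of 0.81 at 34 participants is that of a single sample of pairs and applies neither to the comparison between arms nor to the within-arm tests. For the question the trial poses, power at d = 0.5 is 0.29 unadjusted, so a true medium effect would be missed about 7 times in 10. With baseline adjustment, power is 0.37 to 0.65 for correlations of 0.5 to 0.8 and stays below 80% unless the correlation is about 0.86 or more. The rows for 199 and 15 carry the same error.

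These results assume exactly 17 per arm, complete data, two-sided alpha 0.05, and, for the adjusted figures, d in units of the outcome SD. The mismatch itself rests on no assumption: it follows from the protocol's own test, degrees of freedom and design.

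**What to change.** In Trial design, replace the matched-pairs calculation with one for two independent means with baseline adjustment. State the correlation assumed and its source, and the scale on which d is expressed. Correct or delete the rows for 199 and 15, and bring the Abstract into line.

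If 34 is kept for pragmatic reasons, say so and give the figures that go with it. Power for d = 0.5 is 0.29 unadjusted and about 0.37 to 0.65 for an assumed correlation of 0.5 to 0.8, with about 0.86 needed for 80%. The effect detectable at 80% power is about 0.6 SD (correlation 0.8) to 1.0 SD (unadjusted). If the team can support a higher correlation, it should cite the evidence and extend the range. Add that the trial estimates the effect with a 95% confidence interval, about ±0.70 SD unadjusted, and that a non-significant result will not be reported as absence of benefit. State what loss to follow-up is expected.

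With 34 unchanged, the cost is wording only and no extra participants, but the power claim becomes much weaker. The protocol says that ethical approval is pending and funding still to be sought, so the corrected figures can be before both bodies when they decide. If 80% power for a medium effect is the aim, the trial has to be larger, unless a correlation of about 0.86 or more can be supported.

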
*Treatment-as-usual*

The control group will continue to have access to treatment as usual, which will include medication, input from health professionals and any activities provided in the day hospital if the participant is in attendance. After the completion of the study, participants and their caregivers will be offered a home programme based on the CS-ADL intervention and will be given training in how to use it.

*Outcome measures*

Outcome measures will be recorded in both CS-ADL and TAU participants at baseline (week 0) and post-intervention (week 8). The completion of outcome measures pre- and post-intervention will be mandatory for participation in the trial; participants and caregivers will be reminded of requirements prior to the commencement of the group and after the completion. Socio-demographic information of participants will be collected including age, gender, ethnicity, diagnosis, and medication.

*Primary outcomes: BADL and IADL*

Change in both BADL and IADL will be measured using the Alzheimer's Disease Cooperative Study-Activities of Daily Living (ADCS-ADL) scale (Galasko et al., 1997). This scale was designed for the assessment of ADL outcomes for individuals with Alzheimer's disease in clinical trials. The scale consists of 23 items that includes 6 BADL and 17 IADL outcomes, scored on a range from 0 (patient does not perform the activity), to the highest score (patient is independent in the activity). The scale is administered with caregivers who are asked to rate the degree to which their care-recipient performs each item in the last four weeks (Custodio et al., 2022). The ADCS-ADL has been identified to be a reliable and valid instrument, with high internal consistency and sensitivity to functional changes in individuals with mild-to-moderate dementia (Rózsa et al., 2009).

*Secondary outcomes: Cognition, communication, QOL, mood.*

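### The 34 to be recruited is also the 34 complete pre/post pairs behind the stated power, so that power makes no allowance for loss by week 8

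*Protocol*

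**What the plan says.** The Trial design paragraph of the protocol (Materials and methods) bases its sample size on a matched-pairs t-test with a two-sided alpha of 0.05. For the middle of three effect sizes it reports: "With an estimated effect size of 0.5, a sample size of 34 is required", with "a critical t of 2.0345153 and a df of 33" and "an actual power of 0.8077775". It judges the 199 needed for d = 0.2 impractical and continues: "therefore for pragmatic reasons, recruitment will aim for the sample size of 34". Allocation is 1:1, which makes 17 per arm. The Abstract repeats 34 as the calculated sample size.

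Under Outcome measures, measures are taken in both arms at weeks 0 and 8. Completing them is a condition of taking part, and reminders are planned. The primary outcome, the ADCS-ADL, is rated by the caregiver. The Statistical analysis section plans a linear regression adjusted for baseline, a between-group comparison, and a CONSORT diagram that includes follow-up.

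The protocol gives no expected loss rate, no inflation of the target and no expected number analysed.

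**The concern.** A paired t-test has n − 1 degrees of freedom, so df 33 means 34 complete pre/post differences. The same 34 is then the recruitment target. The two agree only if nobody is lost over eight weeks. Neither making completion mandatory nor planning a reminder produces a score when the caregiver cannot be reached at week 8. Baseline is measured before randomisation, so such a loss can occur only after allocation.

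At stake is how the power statement will be read. A reader would take 0.81 as the power of the trial as recruited, when it is the power with complete data. The omission does not depend on the formula: if the sponsor recalculates for two arms and again quotes the result at 34, that figure will assume zero loss too.

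**Working it through.** **Inputs from the protocol (Trial design):** two-sided alpha 0.05; d = 0.5; 34 participants; 1:1 allocation. **Assumptions, not in the protocol:** loss of 10% or 20% by week 8; a pre-post correlation r = 0.7 for the baseline-adjusted analysis, with d expressed on the raw-score SD.

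**Step 1. Reproduce the stated figure.** For the paired t-test, df = n − 1 and the noncentrality is d√n. With n = 34 this is 0.5 × √34 = 2.915, the critical t is 2.0345 on 33 df, and power is 0.8078. This matches the protocol. Its other two scenarios (199 at d = 0.2, 15 at d = 0.8) also reproduce.

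**Step 2. The same formula with fewer complete pairs.** 34 × 0.90 = 30.6 and 34 × 0.80 = 27.2, taken down to 30 and 27.

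| Pairs analysed | Power, paired formula, d = 0.5 |
|---|---|
| 34 (no loss) | 0.808 |
| 33 (one lost) | 0.795 |
| 31 | 0.768 |
| 30 (about 10% lost) | 0.754 |
| 27 (about 20% lost) | 0.706 |

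The first loss costs 0.808 − 0.795, about 1.2 points before rounding. Losses of about 10% and 20% cost 5.4 and 10.2 points.

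**Step 3. The comparison that is actually planned.** For two arms of n each, unadjusted, df = 2n − 2 and the noncentrality is d√(n/2). With baseline adjustment the noncentrality is divided by √(1 − r²) and one df is lost; at r = 0.7 the divisor is √0.51 = 0.714.

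- No loss, 17 per arm: 0.5 × √8.5 = 1.458; adjusted, 1.458 / 0.714 = 2.041.
- 10% loss, 15.3 per arm: 0.5 × √7.65 = 1.383; adjusted, 1.936.
- 20% loss, 13.6 per arm: 0.5 × √6.8 = 1.304; adjusted, 1.826.

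| Assumed loss | Unadjusted power | Baseline-adjusted power, r = 0.7 |
|---|---|---|
| 0% | 0.293 | 0.507 |
| 10% | 0.267 | 0.464 |
| 20% | 0.241 | 0.418 |

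Fractional arm sizes are kept here. Whole-number splits (15 + 15, 14 + 13) change each figure by less than 0.01.

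**Step 4. Relative size.** Moving from the paired formula to the two-arm comparison costs 0.808 − 0.293 = 0.515 unadjusted, or 0.808 − 0.507 = 0.301 with adjustment at r = 0.7. A 10% loss then costs a further 0.026 or 0.043, and a 20% loss 0.052 or 0.089.

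**The case against.** The strongest objection is that this is a small matter beside the formula. The hypotheses and the planned regression compare two arms, and for that comparison the stated 0.81 does not apply even with complete data. That is right, and it is why the point is secondary and why the remedy must not be another figure from the paired formula. It does not remove the point, because any figure quoted at 34 assumes zero loss.

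It could also be said that attrition belongs in a statistical analysis plan. The handling of missing scores may. But the recruitment target and its power are fixed in the protocol, and that is where the required and recruited numbers are equated.

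A reader might infer more than the protocol supports:

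- *That the stated arithmetic is wrong.* It is not; every stated figure reproduces. What is missing is a planning assumption.
- *That adequate power is lost with the first dropout.* The fall is about 1.2 points. It crosses a threshold only if 0.80 was the target, and the protocol never states one; 0.80 is inferred from achieved powers that all lie just above it.
- *That participant and caregiver must both be available at week 8.* The ADCS-ADL is completed with the caregiver, so a participant who stops attending can still have a primary outcome score.
- *That control participants get no reminder.* The text says "participants and caregivers will be reminded of requirements prior to the commencement of the group and after the completion" and limits this to neither arm; the reference to the group can be read as a calendar marker.
- *That recruiting a few more would repair the design.* Inflating 34 for losses of 5% to 25% gives 36 to 46, which keeps 34 complete pairs for a test that is not the planned comparison.

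**Conclusion.** The point holds in a limited form. The protocol uses 34 both as the number of complete pairs needed and as the number to recruit, with no allowance for loss, so the stated 0.8078 is conditional on a week-8 ADCS-ADL from everyone. On its own formula one loss matters little; about 10% or 20% loss lowers power to 0.754 or 0.706. For the planned between-group comparison the corresponding figures, from no loss to 20% loss, run from about 0.51 to 0.42 with baseline adjustment at r = 0.7, or from about 0.29 to 0.24 unadjusted.

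The loss rates and the correlation are assumptions, since the protocol gives neither. The paired-pairs reading of 34 rests on the stated df and is not in doubt. This should be corrected together with the larger problem of the paired formula.

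**What to change.** In the Trial design paragraph:

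1. State that 34 is the number randomised.
2. Give the number expected to have a week-8 ADCS-ADL, labelled as an assumption (for example 27 to 31).
3. Replace the paired-test power with power, or the smallest detectable difference, at that number for the planned between-group, baseline-adjusted comparison, naming the assumed pre-post correlation. At d = 0.5 and r = 0.7 the text would report about 0.51 with no loss, 0.46 at 10% and 0.42 at 20%.

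Requoting the paired formula at 27 to 31 (0.71 to 0.77) would not do, because it would still describe a different comparison. If the sponsor instead recalculates the sample size for two arms, the loss allowance should be applied to that new number.

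The cost is the rewording of one paragraph and a less favourable stated power. No extra patients are needed, and the reminders and the Abstract can stay as they are for this purpose.
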